### Allocation to study arms

Randomization is performed with an online generated randomization schedule [47], using blocks of six participants for each healthcare center to ensure equal allocations to both arms within and across centers. The randomization schedule is only known and administered by independent researchers who are not involved in the trial in any other way. When participants can be randomized, the independent researchers are informed at which healthcare center the parents are participating and asked to inform the responsible researchers about which condition has been randomly assigned to these parents. Randomization occurs directly after the baseline measurement (T0).

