### Sample size calculation

Based on our previous study that found medium-sized short term effects on daily ratings of behavioral difficulties compared to waitlist (range of Cohen’s *d* = 0.35 to *d* = 0.66, [33]) and studies showing medium-sized parenting intervention effects on behavioral difficulties using parent-report rating scales [19, 20, 25, 36, 72], we estimate the effect of our brief behavioral parent training program as compared to CAU to be at least small (*d* = 0.25).

A power analysis has been performed using G*Power software [73]. Based on an effect size of *d* = 0.25 (*f* = 0.125), two groups and three repeated measures (T0, T1, T2 for short term effectiveness), with *r* = 0.60 between-measurement relation, a power of 0.80 and α = 0.05, we need at least 42 participants per group, resulting in a total of 84 participants. Given that the data are clustered, we increased the sample size with 10% [74], resulting in a total of 93 participants. This is in line with the number of participants in similar studies comparing behavioral treatments to CAU (e.g., [36]).

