### Statistical analysis

Data will be analyzed on an intention-to-treat basis. To examine the effects of the intervention on the primary and secondary outcomes, we will conduct multilevel analyses (mixed modeling), taking missing data into account [75]. Depending on the fit of the models, up to four hierarchical levels will be distinguished: outcomes (level 1), nested within children (level 2), nested within therapists (level 3), nested within healthcare centers (level 4). Random intercepts at the subject level, therapist level and healthcare center level will be included only if the Likelihood Ratio Test shows a significant improvement of the model fit. Time will be included as short-term (T1) and longer-term (T2, T3) within-subjects factors and condition (brief parent training vs. CAU) as between-subjects factor. The interaction between time and condition will be examined to interpret changes over time between conditions. To examine whether the candidate moderator variables moderate the intervention effects, these variables will also be added as interaction effects to the multilevel analyses.

To assess the cost-effectiveness of the brief behavioral parent training compared to CAU, we will calculate the Incremental Cost Effectiveness Ratio (ICER) from a societal perspective. We will perform both a cost-utility analysis (based on QALYs) and cost-effectiveness analyses (based on the daily ratings of behavioral difficulties and based on ECBI-I scores). An ICER is calculated by dividing the difference in the total costs by the difference in the total effect (either QALYs or the daily ratings of behavioral difficulties and ECBI-I scores, respectively). In these analyses, the costs of healthcare will be used and interpolated to the previous 12 months. We will compare each ICER based on relevant willingness to pay thresholds. Bootstrapping will be used to calculate the reliability of our estimates.

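### Reading the effect from a time × condition interaction with an unconstrained baseline amounts to comparing change scores; using the pre-randomisation T0 value would cut the variance by about 20%.

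*Protocol article*

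**What the plan says.** The Statistical analysis section of the protocol article specifies a multilevel model and sets out its fixed part: "Time will be included as short-term (T1) and longer-term (T2, T3) within-subjects factors and condition (brief parent training vs. CAU) as between-subjects factor". It then names the term that carries the intervention effect: "The interaction between time and condition will be examined to interpret changes over time between conditions". The section mentions neither adjustment for the T0 value nor a common T0 mean for the two arms.

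The Sample size calculation section is based on "two groups and three repeated measures (T0, T1, T2 for short term effectiveness"), with "0.60 between-measurement relation, a power of 0.80". T0 is thus one of the outcome occasions.

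The Allocation to study arms section fixes the order of events: "Randomization occurs directly after the baseline measurement (T0"). The Primary outcome section has the daily ratings collected at all four occasions, so every randomised family should have a T0 value.

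**The concern.** A condition main effect together with time × condition lets the two arms have separate means at T0. The T1 × condition coefficient is then the arm difference at T1 minus the whole of the arm difference observed at T0. Randomisation after T0 makes the second quantity zero in expectation, so the model spends information on estimating something the design already settles.

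Two things follow. The standard error is larger than it need be. And a chance imbalance at T0 is subtracted in full, although under the planning correlation only 0.60 of it is expected to persist to follow-up. In a trial of 93 families both effects are large enough to notice. The means of avoiding them, the T0 rating, is already being collected.

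**Working it through.** **Inputs.** From the Sample size calculation section: d = 0.25 (f = 0.125), two groups, three measures, r = 0.60, power 0.80, α = 0.05, 84 participants raised by 10% to 93. Allocation is 1:1 (Study design). The outcome SD is set to 1. The same correlation is assumed between all occasions, and data are taken as complete.

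**The plan's own figure.** For a repeated-measures within-between interaction, λ = f²·N·m/(1 − r) = 0.015625 × 84 × 3 / 0.40 = 9.84, with 2 and (84 − 2) × 2 = 164 degrees of freedom. Power is 0.801; 82 participants give 0.791. So 84 reproduces, and 84 × 1.10 = 92.4 rounds up to 93. Sizing on the between-groups test instead would need 372. The trial was therefore sized on the interaction with T0 as a level.

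**Variance of one follow-up contrast** (per participant, in SD²):
- Change score: 2(1 − r) = 2 × 0.40 = 0.80.
- Baseline-adjusted: 1 − r² = 1 − 0.36 = 0.64.
- Ratio: (1 + r)/2 = 0.80, a variance reduction of 20%. The standard error falls by 1 − √0.80 = 10.6%.

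**Does the stated model really give a change score?** Generalised least squares with 42 per arm gives a variance for the T1 effect of 2 × 0.80/42 = 0.0381 with unconstrained T0 means and 2 × 0.64/42 = 0.0305 with T0 means constrained equal, whether three or four occasions are modelled. In 300 simulated trials fitted with a subject random intercept, the T1 × condition coefficient matched the raw difference in change scores to 3 × 10⁻¹⁵, and the empirical variance ratio was 0.804.

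**Detectable difference at N = 93** (46.5 per arm, 80% power, two-sided 5%, multiplier 2.80):
- Change score: 2.80 × √(2 × 0.80/46.5) = 2.80 × 0.185 = 0.52 SD.
- Adjusted: 2.80 × √(2 × 0.64/46.5) = 2.80 × 0.166 = 0.465 SD.

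Put differently, 93 families analysed with adjustment carry the precision of 93/0.80 ≈ 116 analysed by change score.

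**Sensitivity to r.**

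| r | Change score | Adjusted | Variance reduction |
|---|---|---|---|
| 0.4 | 1.20 | 0.84 | 30% |
| 0.5 | 1.00 | 0.75 | 25% |
| 0.6 | 0.80 | 0.64 | 20% |
| 0.7 | 0.60 | 0.51 | 15% |

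For an effect averaged over p follow-ups, let v = r + (1 − r)/p. The two variances are v + 1 − 2r and v − r². At r = 0.60 these are 0.60 and 0.44 for p = 2 (26.7% reduction), and 0.533 and 0.373 for p = 3 (30%).

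**Chance imbalance.** The standard error of the T0 difference at 46.5 per arm is √(2/46.5) = 0.21 SD. If the arms differ by that much, the change score over-corrects by (1 − 0.60) × 0.21 ≈ 0.08 SD, about one third of the planned d = 0.25.

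**The case against.** The case for leaving the plan alone has real content. Time × condition with T0 as reference is a standard and valid analysis, unbiased under randomisation, and it matches the test on which the sample size was computed. A journal article condenses, and a separate analysis plan could specify how baseline enters. The 20% is a variance figure. On the scale of the T1 contrast at d = 0.25 with 42 per arm, power moves only from 24.9% to 29.9%. The identity with a change score is exact only for complete data with a subject random intercept. The article makes that intercept conditional on a likelihood ratio test and, in its Discussion, anticipates dropout.

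Most of this stands as a limit on size, and none of it removes the point. The article does more than stay silent: it names the factors and the term to be examined, and that model as written has separate T0 means. A later plan may improve on it, but this is the model on record.

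A reader might also infer something stronger from the time factor, which lists T1, T2 and T3 but not T0. If only those occasions were modelled, the interaction would be zero for a constant benefit and could not detect a sustained effect. The documents do not support that reading. The sample size section names T0 as a repeated measure, 84 reproduces on that basis, and the stated aim is to interpret change over time. It would also be incompatible with the point made here, which needs T0 among the responses. What remains is a wording gap between the two sections.

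**Conclusion.** The point holds as one of efficiency and chance imbalance, not of validity. At r = 0.60 the planned contrast at a single follow-up gives up 20% of the available information, equivalent to a detectable difference of 0.52 instead of 0.465 SD at 93 families. The range is 30% to 15% for r from 0.4 to 0.7.

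This rests on T0 being a response level, equal correlation between occasions and complete data; with missing ratings the figures are approximate. It ignores clustering by therapist and centre.

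One might be tempted to conclude from a detectable 0.52 SD against a planned 0.25 that 84 or 93 is wrong. That does not follow from this point: the stated number agrees with the overall interaction test at the f the authors entered, whereas 0.52 belongs to a single T1 contrast. Whether that f is a suitable target is a separate question. The change is worth making because it is a better use of data already in hand.

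**What to change.** Choose one of two models for the primary outcome:

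1. Keep T0 to T3 as responses and constrain the T0 mean to be equal across arms: no condition main effect, only condition × T1, condition × T2 and condition × T3.
2. Use T1 to T3 as responses, with T0 as a covariate, condition, time and condition × time.

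Report the adjusted arm differences at T1, T2 and T3 with confidence intervals. Do the same for each secondary outcome that has a T0 value, at whichever follow-ups it is measured. In the same sentence, say whether T0 is the reference level or the covariate, so that the Statistical analysis and Sample size calculation sections agree.

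No new data, visits or participants are needed. The cost is a documented amendment, since the effect term of a registered trial changes; it should be dated before outcome data are examined by arm.

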### Objectives and hypotheses

The first objective of this study is to examine the short- and longer-term (i.e., one year) effectiveness of the brief and individually tailored behavioral parent training program with optional booster sessions compared to care as usual (CAU) on daily measured child behavioral difficulties (primary outcome) and on a range of secondary outcomes (see Outcomes). Additionally, we will explore whether a number of general demographic and clinical characteristics, parental attachment, parental psychopathology, parental reward responsivity, and reward and punishment sensitivity of the child moderate the short- and longer-term intervention effects on our primary outcome. The second objective is to investigate the cost-effectiveness of the program compared to CAU. As we assess cost-effectiveness based on measures at baseline and one year after the intervention, we can only draw conclusions about the cost-effectiveness on the longer term.

Based on our earlier work [33, 35], we hypothesize that the brief behavioral parent training with booster sessions will be more effective than CAU in reducing children’s behavioral difficulties. Consequently, we expect parents who receive the brief behavioral parent training to use less subsequent care and thus hypothesize the brief training to be more cost-effective than CAU on the longer term.

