##### Use of healthcare

Use of mental healthcare within the organization where the child is treated is measured by drawing up an inventory (based on patient records) of the type of care (brief behavioral parent training, booster sessions, CAU) that is used and the duration (in minutes) of this care between T0 and T3 in both arms. The broader use of healthcare within and outside the mental healthcare centers is assessed with the *Vragenlijst Intensieve Jeugdzorg*, a Dutch questionnaire on intensive youth care [60]. This questionnaire assesses the use of a wide variety of healthcare (e.g., contact with general practitioner or medical professionals, use of social services or (alternative) medicines), along with the child’s use of education, contact with judicial authorities, and losses in the productivity of parents. Parents complete this questionnaire about the use and intensity of healthcare of both the child and themselves in the past three months. This outcome is measured at T0 and T3. Both measures of healthcare use (i.e., inventory of care and questionnaire) will be combined to obtain a complete image of all used care.

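### The ICER's cost term is given as a difference in total costs with no stated role for the baseline care-use questionnaire; the incremental cost should be adjusted for it

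*Protocol article*

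**What the plan says.** The Statistical analysis section of the protocol article gives three elements of the economic estimator:

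- The ratio: "An ICER is calculated by dividing the difference in the total costs by the difference in the total effect".
- The cost window: "In these analyses, the costs of healthcare will be used and interpolated to the previous 12 months".
- The uncertainty method: "Bootstrapping will be used to calculate the reliability of our estimates".

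It names no regression model and no covariate for costs.

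The Use of healthcare section describes two sources of resource use. One is a questionnaire covering care, the child's education, judicial contacts and parents' productivity losses: "Parents complete this questionnaire about the use and intensity of healthcare of both the child and themselves in the past three months". On its timing and use the section says: "This outcome is measured at T0 and T3. Both measures of healthcare use (i.e., inventory of care and questionnaire) will be combined". The other source is an inventory from patient records, which covers "the duration (in minutes) of this care between T0 and T3 in both arms".

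The section on allocation places randomisation directly after T0 and describes the schedule as "using blocks of six participants for each healthcare center". Prior care use is not a stratification factor.

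The objectives add one sentence on baseline: "As we assess cost-effectiveness based on measures at baseline and one year after the intervention", conclusions are limited to the longer term. How the baseline measures enter is not said there or elsewhere.

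**The concern.** A pre-randomisation measure of resource use exists for the questionnaire items, but the description of the cost contrast does not use it. If the contrast is computed as described, two things follow.

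First, families with high prior use of care, special schooling or lost work can fall unevenly between the arms by chance. To the extent that such use persists, the imbalance reappears in follow-up costs and moves the estimated cost difference.

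Second, precision that the T0 data could supply is left unused.

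The cost contrast matters because the trial hypothesises that trained families will need less later care and that the program will therefore be more cost-effective. The sign of the cost difference decides the quadrant of the cost-effectiveness plane. Costs are usually skewed, and the trial is small for this purpose. The point concerns the cost numerator only, not the effect denominator and not the primary effectiveness analysis.

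**Working it through.** **Inputs.** The total of 93 families and 1:1 allocation are from the protocol article, giving 47 and 46 per arm. The cost SD and rho are not in the documents. Results are therefore in SD units and rho is an assumed range. All 93 families are taken to supply cost data, with equal spread in both arms.

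**1. The plan's own figure.** The article gives no sample size for costs. Its calculation for the primary outcome uses f = 0.125, two groups, three measurements and r = 0.60. The noncentrality is f² × N × m / (1 − r) = 0.015625 × 84 × 3 / 0.40 = 9.84, with 2 and 164 degrees of freedom. Power is 0.801, so 84 is reproduced. 84 × 1.10 = 92.4, rounded up to 93. This supplies N and has no other bearing on the cost analysis.

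**2. Size of a chance T0 imbalance.** SD = sqrt(1/47 + 1/46) = 0.207, and the 95% range is ±1.96 × 0.207 = ±0.41 SD. The chance of an imbalance above 0.2 SD in either direction is about 33%, and above 0.3 SD about 15%. The same 0.207 SD is the standard error of the unadjusted cost difference.

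**3. Effect of adjusting for T0 cost.** Carried shift = rho × imbalance. Adjusted SE = 0.207 × sqrt(1 − rho²). Variance reduction = rho². Equivalent unadjusted N = 93 / (1 − rho²).

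| rho (assumed) | Variance reduction | Adjusted SE | Interval narrower by | Equivalent N | Shift from 0.2 SD imbalance | Shift from 0.41 SD imbalance |
|---|---|---|---|---|---|---|
| 0.1 | 1% | 0.206 | 0.5% | 94 | 0.02 | 0.04 |
| 0.3 | 9% | 0.198 | 4.6% | 102 | 0.06 | 0.12 |
| 0.5 | 25% | 0.180 | 13.4% | 124 | 0.10 | 0.20 |
| 0.7 | 49% | 0.148 | 28.6% | 182 | 0.14 | 0.28 |

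The last column uses an imbalance at the edge of its 95% range, so it is an upper case and not a typical one.

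**4. Skewed costs.** In a simulation with lognormal costs and 93 families, both estimators were centred near zero when there was no effect. Adjustment lowered the standard error by about 2%, 10% and 15% at mean sample correlations of 0.22, 0.41 and 0.50. The gain thus survives skewness.

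**5. If baseline enters as a change score.** The sentence in the objectives could be read this way. With equal variances at the two times, the variance relative to the unadjusted difference is 2(1 − rho): 1.4 at rho = 0.3, 1.0 at 0.5 and 0.6 at 0.7. Under regression adjustment it is 1 − rho²: 0.91, 0.75 and 0.51. The gap is (1 − rho)², which is never negative. So how baseline enters matters, and regression adjustment is at least as precise as either alternative, apart from the degree of freedom it uses.

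**The case against.** The strongest reply is that the quoted sentence is the generic definition of an ICER. It fits a regression-adjusted cost difference as well as a simple one, and the words raw and unadjusted do not appear. The article is condensed, and the covariates of a cost model are often left to an analysis plan, which is not shown here. This stands against any claim that the plan has chosen an unadjusted analysis. It does not remove the point. The article states the formula, the window and the uncertainty method, and it describes the clinical model down to its random intercepts, yet it gives the T0 questionnaire no role in the cost contrast.

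A reader might infer three stronger things that the documents do not support:

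- **That the plan discards the baseline cost data.** The objectives say that baseline measures are used; only the manner is unstated.
- **That chance imbalance biases the cost result.** The unadjusted difference is unbiased over randomisations, and the bootstrap interval already reflects its variability. In the one trial that is run, the interval is wider but is not recentred for the imbalance observed.
- **That every cost component has a baseline value.** Only the three-month questionnaire does. The record inventory starts at T0. A covariate need not match the outcome item for item, so the questionnaire-based cost still serves.

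Rho may also be low. Families are recruited before treatment starts, and children on current or recent psychotropic medication are excluded, as are parents who had behavioral parent training in the past year. Schooling, judicial contacts and productivity losses are not restricted in this way, but their share of total cost is unknown.

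**Conclusion.** The concern holds in a limited form. The article states the cost term as a difference in total costs with bootstrapped uncertainty and assigns no stated role to the T0 care-use questionnaire. If followed as written, the contrast is unbiased, but it is less precise than the collected data allow and open to chance T0 imbalance. At 93 families the standard error is about 0.21 SD. The variance that could be removed runs from about 1% at rho = 0.1 to 49% at rho = 0.7. That range rests wholly on an assumed rho, and at 0.2 or below the gain is negligible (4% of variance at 0.2). The change is still worth making, because it is cheap and because unadjusted, change-score and adjusted contrasts can differ in sign in a trial of this size. The choice should be fixed before the data are seen.

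**What to change.** State in the economic analysis that the incremental cost is the arm coefficient from a regression of follow-up cost on arm, T0 questionnaire-based cost and center. Fit it within each bootstrap sample, jointly with the effect equation (for example by seemingly unrelated regressions), so that the correlation between costs and effects is kept. Say explicitly that the T0 covariate comes from the questionnaire alone, because the record inventory has no value before T0. Report the unadjusted cost difference alongside.

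The cost is about one sentence in the plan and slight extra analysis work. No new data are needed, since the T0 questionnaire is already part of the baseline measurement. The downside is little gain if rho is low.

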### Procedure

Parents in the brief behavioral parent training arm receive three sessions of behavioral parent training. The first two sessions take 120 min each and are planned one or two weeks apart. The third session takes 60 min and is planned one week after the second session. To take parents’ and therapists’ availability into account, some flexibility in planning is allowed as long as all three sessions are planned within six weeks with at least one week between two consecutive sessions. After the third session, parents wishing to receive additional support can receive CAU and/or booster sessions. The booster sessions take 60 min each and can be provided maximally once every four weeks up to one year after the last session of the brief behavioral parent training program. Booster sessions can be suggested by the therapist who provided the brief behavioral parent training or by other involved clinicians, or requested by parents themselves.

The trial contains four measurement occasions, see Fig. 1 for the participant timeline. T0 takes place after parents provide consent and are found eligible for participation, before randomization. The first posttreatment measurement (T1) takes place one week after the third session for parents in the brief behavioral parent training arm and eight weeks after T0 for parents in the CAU arm. The second posttreatment measurement (T2) takes place six months after T1 and the third posttreatment measurement (T3) takes place twelve months after T1. Participation in the trial therefore takes approximately 14 months in total. The care families receive at the child mental healthcare center may terminate sooner if they do not need or want care anymore.

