##### Utilities

Utilities, also called preferred health states, are assessed using quality-adjusted life years (QALYs). QALYs range between 0 and 1, where 0 represents death and 1 perfect health. QALYs are calculated based on the EuroQol-5D-5L (EQ-5D) questionnaire [57, 58], which parents fill out about their child. The EuroQol-5D-5L measures the child’s health with five items (mobility, self-care, daily activities, pain, and anxiety/depression) on 5-level categorical scales. EQ-5D responses will be transferred into QALYs based on the Dutch EQ-5D-5L tariff for adults [59], as a tariff for Dutch children is not yet available. The content and face validity of the EuroQol-5D-5L are well established [58]. This outcome is measured at T0 and T3.

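### The 12-month cost window conflicts with the T0–T3 care inventory, and QALYs rest on a utility measured only at T0 and T3

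*Protocol article*

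**What the plan says.** All references are to the protocol article.

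- **Statistical analysis.** The ICER divides the difference in total costs by the difference in total effect, from a societal perspective. For the numerator, "the costs of healthcare will be used and interpolated to the previous 12 months". The section does not say which cost items this covers.
- **Use of healthcare, records.** A patient-record inventory lists the type of in-centre care, naming the brief training, booster sessions and CAU, "that is used and the duration (in minutes) of this care between T0 and T3 in both arms".
- **Use of healthcare, questionnaire.** "The broader use of healthcare within and outside the mental healthcare centers is assessed" by a parent questionnaire that also covers education, justice contacts and parents' productivity losses. On recall: "Parents complete this questionnaire about the use and intensity of healthcare of both the child and themselves in the past three months". On timing: "This outcome is measured at T0 and T3". The two sources are to be combined, with no rule for care that appears in both.
- **Utilities.** EQ-5D-5L answers are converted with the Dutch adult tariff, also at T0 and T3 only. The result is described thus: "QALYs range between 0 and 1, where 0 represents death and 1 perfect health".
- **Procedure.** T1 is eight weeks after T0 in the CAU arm and a week after session three in the training arm. T3 is 12 months later than T1. "Participation in the trial therefore takes approximately 14 months in total".
- **Study design.** The training arm may not receive CAU until T1; the CAU arm has no such restriction.

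**The concern.** An ICER is interpretable only if costs and effects accumulate over the same period in both arms. Here the stated cost window (12 months back from T3) and the stated inventory period (T0–T3) differ, and the difference is the interval in which the intervention is delivered. The two possible readings of the rule give different numerators.

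That interval is also where the design forces care use to differ between arms, because CAU is closed to one arm and open to the other. For outside care and productivity, the only post-baseline observation is the last three months. By then boosters and CAU have long been available to the training arm, so that quarter is a weak guide to the earlier period.

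On the effect side, a tariff value is a utility at one moment and a QALY is utility accumulated over time. With utility known only at the two ends, the accumulated difference is set by an assumed path. The Background section itself reports sustained, fading and sleeper effects for parent training, so no single path can be taken as given. Cost-effectiveness is the trial's second objective.

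**Working it through.** **Follow-up length.** Eight weeks = 56 / 30.4375 = 1.84 months. T0–T3 = 1.84 + 12 = 13.84 months, which reproduces the protocol's figure of about 14. Eight weeks is fixed only for the CAU arm. For the training arm T0–T1 depends on scheduling, and I assume the same length.

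**Cost window.**
- Twelve months back from T3 is T1–T3. Omitted: 1.84 / 13.84 = 13.3% of follow-up.
- Core training inside the omitted period: 120 + 120 + 60 = 300 minutes, i.e. all of it.
- If the rule cut every cost, the share of training-plus-booster minutes lost would be 300 / 300 = 100% with no booster, 300 / 360 = 83% with one and 300 / 420 = 71% with two.
- Observed by the questionnaire after baseline: 3 / 13.84 = 21.7%. Simple scaling to 12 months implies a factor of 12 / 3 = 4, and to T0–T3 a factor of 13.84 / 3 = 4.6. The protocol states no factor; these follow from the windows.
- The T0 questionnaire looks back before T0, so T0–T1 is unobserved for outside costs on any reading.

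**QALYs.** Let Δu be the peak between-arm utility difference, zero at T0. The reference is the trapezoidal area over T0, T1, T2 and T3, in years. The two-point figure joins T0 to T3 by a straight line.

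| Course of the difference | Area under the curve | Two-point line | Captured |
|---|---|---|---|
| Reached at T1, sustained | (0.5×1.84 + 12)/12 = 1.077Δu | 0.5×13.84/12 = 0.577Δu | 54% |
| Reached at T1, fades linearly to zero at T3 | (0.5×1.84 + 0.5×12)/12 = 0.577Δu | 0 | 0% |
| Grows linearly T0 to T3 | 0.577Δu | 0.577Δu | 100% |
| Arises only between T2 and T3 | 0.5×6/12 = 0.25Δu | 0.577Δu | 231% |

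The percentages do not depend on Δu. For illustration only, with Δu from 0.02 to 0.05 (an assumption; the documents give no value), the sustained case is 0.0215 to 0.0538 QALY against 0.0115 to 0.0288 by two points.

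**Definition.** Full health over T0–T3 is 13.84 / 12 = 1.15 QALYs, so a ceiling of 1 does not fit that horizon. It would fit 12 months, but a T1–T3 effect window needs a utility at T1, which is not collected. If the T3 tariff value were itself used as the QALY, the four courses would give Δu, 0, Δu and Δu, which again does not match the areas.

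**The case against.** The strongest reply is that the inventory explicitly lists the brief training over the whole of T0–T3, and that a continuous record needs no interpolation. The rule then naturally applies only to the questionnaire. A reader might infer from the 12-month wording that the training period is not costed at all; the documents do not support that as fact. The data are to be collected, and the loss occurs only if the rule is applied to every cost. What remains is that the sentence carries no such limit, and that the narrower reading still combines a window of about 14 months with one of 12.

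A reader might also infer that in-centre care is counted twice. The text says the sources are combined for completeness, not added, and a rule for overlap may sit in a fuller plan. Double counting is a risk arising from overlapping scopes, not a stated procedure.

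A third tempting inference is that QALY gains between T0 and T3 are lost. Only a gain gone by T3 is wholly lost; a linear one is fully captured and a late one is overstated, so the bias has no fixed direction. The Objectives section also discloses that cost-effectiveness rests on baseline and one year and supports longer-term conclusions only. That is a partial answer: it admits the sparse measurement, but an ICER of total costs over total effect still needs a common period.

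Finally, the accumulation formula for QALYs is ordinary analysis-plan content. That is fair for the formula, but not for the measurement times, which are set here and cannot be repaired later by analysis. The cost-effectiveness analyses on daily ratings and ECBI-I use outcomes measured at all four visits, so the utility point does not reach their effect side.

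**Conclusion.** The concern holds in a limited form. The 12-month rule and the T0–T3 inventory do not share a window. Depending on the reading, the cost numerator either drops T0–T1 (about 1.8 months, 13% of follow-up, with all 300 minutes of core training) or mixes windows and extrapolates outside-care and productivity costs from 22% of follow-up, with T0–T1 unobserved. Overlap between the two sources leaves double counting possible.

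The QALY is described as a tariff value and observed at two points only. The accumulated difference therefore depends on an unobserved path, with capture from 0% through 54% and 100% to an overstatement.

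This rests on an eight-week T0–T1 interval in both arms, on simple proportional scaling, and on straight-line joining of two utilities, none of which the protocol spells out. It affects the second objective; the primary outcome and its analysis are unaffected.

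**What to change.** Before the economic analysis, amend the wording as follows:

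1. Use one window, T0–T3, for costs and effects in both arms.
2. Take all in-centre care, including the three sessions and the boosters, unscaled from the patient records.
3. Use the questionnaire only for care and losses outside the centre, which also removes the overlap. Extrapolate these to the same T0–T3 window, with a sensitivity analysis on the extrapolation.
4. Call the tariff value a utility, and define QALYs as the area under the utility curve over T0–T3. Add sensitivity analyses on the path: early and sustained, fading, linear and late.
5. As a cheap addition, collect the five EQ-5D-5L items at T1 and T2 from families who have not yet reached those visits.

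Items 1 to 4 change wording and analysis only. Item 5 adds a slight burden per visit, and these points will be missing for earlier enrollees, so the analyses under item 4 are needed in any case.
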